## Abstract

**Background:**

Due to its rising prevalence type 2 diabetes plays an important role concerning population health in Austria and other western countries. In various studies deficiencies in the care of diabetic patients have been revealed. These deficiencies may be overcome by disease-management-programmes (DMPs), but international experience shows that the effectiveness of DMPs is inconsistent. In particular large programmes designed by state-affiliated public health insurances have not been evaluated in randomized controlled trials (RCTs). We are therefore conducting a large scale RCT of the Austrian DMP for type 2 diabetic patients in the province of Salzburg to evaluate the programme regarding its effects on metabolic control, guideline adherent care and the quality of life of diabetic patients.

**Methods/Design:**

The study is open for participation to all GPs and internists in the province of Salzburg. Physicians are randomized before recruitment of patients with the districts of Salzburg as clusters of randomisation. A total of over 1200 patients with type 2 diabetes will then be recruited. In the intervention group the DMP is applied for one year. Controls receive usual care. Endpoints are a decrease in HbA1c in the intervention group > 0,5% compared to controls, a higher percentage of patients with required diagnostic measures according to guidelines, improved cardiovascular risk profile and higher quality of life scores within one year.

**Current status of the study:**

98 Physicians agreed to participate in the study. 96 of them recruited 1494 patients, 654 in the intervention and 840 in the control group.

**Trail Registration:**

This trial has been registered with Current Controlled Trials Ltd. (ISRCTN27414162).

## Background

The prevalence of type 2 diabetes is rising worldwide [1]. In Austria about 3,5 – 5% of the population are affected and it has been shown that diabetes care is insufficient [2]. The socioeconomic impact of the disease is alarming and it is necessary to improve its prevention and control. Effective screening for early detection and structured care according to current guidelines are the most promising strategies to avoid diabetic complications. One of the concepts to assure optimized care is the design of disease management programmes comprising physician training in guideline-adherent therapy and patient education as well as reminders and continuous feedback. Unfortunately disease management programmes don't seem to guarantee optimum care. As has been shown in Germany, a nation-wide implementation of DMPs by mandatory public health insurances may rather lead to increasing bureaucracy than to an improvement in care. Therefore the programmes have been criticized widely [3]. Evaluation studies have not been carried out as randomized controlled trials, and have been restricted to small samples of highly motivated physicians. Thus, results so far are not sufficient to support a general implementation [4]. Randomized controlled trials that have been performed in various countries have never evaluated large programmes of state-affiliated public health insurances, and showed only limited success, especially regarding clinically relevant endpoints. DMPs may – depending on the programme – improve surrogate parameters like HbA1c, but didn't show any effect on cardiovascular morbidity and mortality after six years of observation [5].

In a systematic review the authors conclude that the majority of DMPs lead to an improvement in metabolic control, but this appears to be largely dependent on the individual programme and its particular design [6]. Thus, physician training leads to an improvement of metabolic control only in 38% of the studies included in the review, and to increased guideline adherence in 50% of the studies. Patient education was shown to be effective in 44% of the studies.

Another systematic review published in 2004 came up with similar results. Only in 24 out of 66 randomized controlled trials on the effectiveness of DMPs a significant improvement in patient care and metabolic control was demonstrated [7].

One systematic review achieved slightly better results but included non-controlled studies as well as studies performed in HMOs (Health Maintenance Organisations) and Community Clinics. The results can hardly be transferred to single GP surgeries [8].

The effectiveness of patient education has been explicitly evaluated in a Cochrane-Review. The authors conclude with caution that patient education in groups may tend to improve metabolic control. 10 out of the 11 studies included in the review are considered to have serious methodological deficits [9]. Among these the study of Pieber et al. is also criticised. The development of the DMP of the Austrian Public Health Insurance has been partly based on this study. It is characterised by non-randomized controls, a short observation period and a small number of highly motivated surgeries [10].

All these reviews show clearly that there are large discrepancies and variations from study to study regarding the effectiveness of a DMP. One of the explanations may be that there are important differences in the design, making each DMP a unique intervention in a unique setting that may not be comparable to other DMPs even though the basic elements (physician training, patient education, reminders etc.) remain the same. We therefore believe that a newly designed DMP must be evaluated in its particular setting before general implementation can be recommended. This is especially true for large public programmes that not only impose additional work on the surgeries involved but also cause tremendous cost to the health care system.

The prerequisites of summative evaluation of public health interventions have been described in the context of international expertise and comprise the performance of a randomized controlled trial prior or at least parallel to their general implementation [11]. In several instances, i.e. in the implementation process of DMPs by public health insurances in Germany this rigorous evaluation has not been performed, leading to persistent criticism and scepticism regarding the effectiveness of these programmes [12]. Now a summative and controlled evaluation is not possible anymore because the programmes have been implemented all over the country.

In Austria we are currently facing the plan of a nationwide implementation of a DMP for type 2 diabetes. To avoid the lack of a summative evaluation as presently missing in Germany we suggested to the public health insurance and health authorities of Salzburg to implement the DMP starting with a RCT.

## Objectives of the study

The study focuses on the following aspects of effectiveness of the DMP for type 2 diabetic patients (called „Therapie aktiv“) designed by the Austrian public health insurance:

• Does metabolic control improve in type 2 diabetics participating in the DMP „Therapie aktiv“ compared to controls receiving usual care after one year of observation?

• Is guideline-adherent care regarding metabolic control and early detection of diabetic complications improved in DMP-patients compared to controls receiving usual care?

• Is guideline-adherent therapy of type 2 diabetes and its complications improved in DMP-patients compared to controls receiving usual care?

• Is guideline-adherent therapy of cardiovascular risk factors improved in DMP-patients compared to controls receiving usual care?

The primary objective of the study is to show that the Austrian DMP for diabetes mellitus type 2 improves metabolic control of patients with diabetes. This improvement must exceed a decrease of HbA1c of 0.5% between the beginning and the end of the study in the intervention group compared to the controls (see endpoints).

Secondary objectives are to demonstrate that the Austrian DMP leads to an improvement of guideline adherent treatment and an increased frequency of the recommended preventive examinations regarding diabetic complications (i.e. frequency of eye examinations, foot examinations, testing for microalbuminuria, serum creatinine and plasma lipids). Another secondary objective of the study is the calculation of the effect of the DMP on economic issues (i.e. prospective hospital admissions and economic burden due to diabetic complications).

## Methods/Design

### Study Design

The study is performed as a cluster-randomized controlled trial of a complex intervention with an observation time of one year. Randomization-clusters are the districts of the province of Salzburg because randomization is neither feasible at the level of the patient nor at the level of the GP. Randomization at the level of the patient leads to the problem that a single GP would have to treat some patients according to usual care and others according to the DMP which is hardly possible because of "contamination" effects. Also, randomization at the level of the GP appears not to be advisable, because this would lead to contamination effects especially in rural areas, where neighbouring GPs have overlapping patient groups. Patients knowing one another and belonging one to the intervention and the other to the control group, may even switch their physician.

### Setting and Study Population

The study takes place in the province of Salzburg, consisting of Salzburg city with about 150.000 inhabitants and five districts (suburban and rural areas including a few larger villages with a total of about 350.000 inhabitants. The prevalence of type 2 diabetes in this population is estimated to be about 2.5 to 3%.

### Recruitment and Randomization

#### Recruitment of the surgeries

Participation in the study is offered to all physicians who are eligible to participate in the DMP, i.e. all GPs and specialists in internal medicine with their own surgery and a contract with the public health insurance (252 GPs and 23 specialists in internal medicine). We inform all of the 275 physicians in writing about the study and its objectives and ask them to respond by letter or fax to declare their willingness to participate. Furthermore, we offer additional information by phone. All physicians are informed explicitly that the study will be a randomized controlled trial, and that randomization will only take place after a commitment to participate has been made. Therefore, at the time of signing up the physicians do not know which group – intervention or control – they will belong to.

#### Randomisation

Randomisation takes place at the level of the districts after completion of physician recruitment. The city of Salzburg as the only urban region of the province is divided into two study districts (one being to the right, the other to the left of the Salzach, the river that divides the city in nearly two halves). To assure even distribution of the districts regarding population characteristics and size the districts are randomized as matched pairs. Salzburg city to the right of the Salzach is matched with the city left of the Salzach, the district Pongau is matched with Pinzgau and Lungau (mostly mountainous regions with remote villages), and the district Flachgau is matched with Tennengau (both adjacent to Salzburg city with partially suburban and partially agricultural regions, more densely populated than the mountain districts). The randomization process is performed under the supervision of a committee comprising representatives of Paracelsus University, the Austrian public health insurance, the Working-group for Preventive Medicine, Salzburg (AVOS) and the healthcare department of the government of the province.

#### Recruitment of patients

All patients (> 18 years) with type 2 diabetes that fulfil the WHO/ADA-criteria for diabetes diagnosis are eligible to participate in the study. The physicians are encouraged to continuously recruit all patients with type 2 diabetes that enter the surgery during the recruitment period (from July 1^st ^to October 31^st ^of 2007). All patients willing to participate are included in the study after informed consent according to the declaration of Helsinki.

Exclusion criteria are dementia/psychiatric illness with inability to participate or to give informed consent, or known major consuming illness (i.e. advanced cancer).

### Intervention

In the intervention group the complex intervention of the DMP for type 2 diabetes as designed by the Austrian public health insurance ("Therapie aktiv") is applied, consisting of:

• a 10-hour training course for all physicians of the intervention group as designed by the Austrian Diabetes Association (ÖDG), the Austrian Medical College (Ärztekammer), and the Austrian Society for General Practice (ÖGAM). Physicians are trained by experienced GPs and specialists from the diabetes unit of the Medical Department I of the University Hospital Salzburg, and from the Institute of General Practice, Family Medicine and Prevention, both of Paracelsus Medical University (PMU)

• 9 hours of patient-education in 4 modules with a group size of 3 to 12 patients. Patient education is organized by the Workgroup for preventive medicine Salzburg (AVOS) according to the curriculum of the „Düsseldorfer Modell“ [13] and performed by especially trained physicians in their surgeries or in hospital out-patient clinics. The modules have been offered all over the province long before the implementation of the DMP (i.e. the study) but have not been used widely enough.

• documentation in a DMP-form at the beginning and at the end of the study year.

• structured interdisciplinary care as prescribed in the DMP according to the guidelines of the Austrian Diabetes Association (ÖDG).

• patient and physician reminders every three months sent out by the public health insurance to assure adherence to the schedule of prescribed diagnostic and therapeutic measures.

• agreement on therapeutic goals in a shared decision-making process of patient and physician.

### Control

In the control group the physicians perform the standard care as prescribed by current guidelines for the management of type 2 diabetes. Continuous medical education and patient education are allowed at the discretion of the particular physician or patient.

### Documentation and Monitoring

#### Baseline-Examination

At inclusion the following parameters are examined and recorded:

**• Laboratory**: Fasting and postprandial blood glucose, HbA1c, cholesterol, triglycerides, HDL-cholesterol

**• Anthropometric measurements**: Height and body weight, systolic and diastolic blood pressure

**• Case Report Form**: In the intervention group the DMP documentation form is used. To avoid bias, a simplified case report form is used in the control group. Some parameters (i.e. known diabetic complications) will be registered at the end of the study, see below).

#### Final examination

After one year baseline data will be recorded once again. In an additional case report form diabetic complications (present already at the beginning, and those that arose during the year), cardiovascular events, hospitalization, hypoglycaemias, diagnostic and therapeutic measures as well as therapeutic goals will be recorded (i.e. ophthalmological, neurological, podological, and nephrological examinations). Quality of life will be evaluated with the German version of the EQ-5 which has been used in the UKPDS (Version EQ5-D) [14].

### Endpoints

The primary endpoint of the trial will be the change in HbA1c from baseline to 12 months (final examination). Secondary outcomes will include a reduction in the amount of time spent in a hospital during the year of the study, a higher percentage of patients with guideline adherent diagnostic and therapeutic measures (i.e. eye examination, foot examination frequency) during the study, as well as improved control of cardiovascular risk and a higher EQ5-D-score in the intervention group at the end of the study.

The differences between the intervention group and the control group regarding primary and secondary endpoints will allow an estimate of the impact of the DMP on health economics.

### Data management and calculation of sample size

All data are recorded in the surgeries of the participating physicians and then transferred to the Institute of General Practice, Family Medicine and Prevention of the PMU for further processing and evaluation.

Sample size was calculated using the primary endpoint, i.e. the change in HbA1c from baseline to final examination at 12 months. Using an estimate of standard deviation for HbA1c change of 2%, a total of 504 patients (252 per arm) would be required to detect a difference of HbA1c of 0.5% (effect size, 0.25) with a power of 1-β = 80% using a two-sided two-sample t-test at a 0.05 significance level. Assuming an intracluster correlation coefficient of 0.05 and an average cluster size of 20, we estimated a design effect of D = 1 + (20-1) × 0.05 = 1.95. Thus, to have adequate power, the sample size had to be increased to 984 patients (492 per arm). Assuming a drop-out-rate of 20%, the sample size was adjusted to 615 patients per arm, or a total of 1230 patients.

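### The 80% power rests on a design effect for clusters of 20 patients, but six district units are randomised, so the power claim is unsupported as written

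*Protocol article*

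**What the plan says.** **Unit of randomisation.** Under Study Design the article states: "Randomization-clusters are the districts of the province of Salzburg". It rejects randomising patients or GPs. Under Randomisation, "the districts are randomized as matched pairs": city right with city left of the river, Pongau with Pinzgau plus Lungau, and Flachgau with Tennengau. Current status of the study confirms that Pinzgau and Lungau went to the same arm. There are seven named areas but six allocation units, three per arm.

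**Sample size.** Under Data management and calculation of sample size the article starts from "a total of 504 patients (252 per arm) would be required" and then writes: "Assuming an intracluster correlation coefficient of 0.05 and an average cluster size of 20, we estimated a design effect of D" = 1.95. That gives 492 per arm, and 615 per arm after 20% drop-out. The level to which the cluster of 20 belongs is not named.

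**Analysis.** Statistical Analysis plans mixed models that allow for clustering, without naming the level. The Discussion concedes that cluster effects may be underestimated and promises to analyse them, but leaves the sample size and power as they were.

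**The concern.** Twenty cannot be the size of a district unit. At 20 per cluster, 984 patients make about 49 clusters (984/20), whereas six units were randomised. Only a surgery is of that order: 1494 patients from 96 recruiting physicians is 15.6 each. That the cluster of 20 is a surgery is therefore an inference, though the likely one.

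If so, the design effect covers similarity of patients within a surgery and leaves out similarity within a district, which is the level at which treatment was assigned. It also takes the t-test's degrees of freedom from hundreds of patients, while a comparison of six units has 4, or 2 if analysed as three pairs.

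At stake is how a null result is read. The Conclusion argues that failure of the programme in this study would settle the matter for less motivated physicians. That inference needs the stated power to be real.

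**Working it through.** **Inputs from the article**
- Endpoint: "The primary endpoint of the trial will be the change in HbA1c from baseline to 12 months (final examination").
- Variability: "Using an estimate of standard deviation for HbA1c change of 2" percentage points.
- Target: "to detect a difference of HbA1c of 0.5% (effect size, 0.25").
- Test: "with a power of 1-β = 80% using a two-sided two-sample t-test at a 0.05 significance level".
- ICC 0.05, cluster size 20, drop-out 20%.
- Recruited: 654 and 840, total 1494, from 96 physicians.

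**Step 1. The stated figures reproduce.**
- n = 2(1.96 + 0.84)²/0.25² ≈ 251, or 252 per arm with unrounded quantiles.
- D = 1 + 19 × 0.05 = 1.95.
- 252 × 1.95 = 491.4, so 492.
- 492/0.8 = 615 per arm, 1230 in total.

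**Step 2. Size of the randomised unit.** 984/6 = 164 analysed; 1230/6 = 205 planned at entry; 1494/6 = 249 recruited.

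**Step 3. District clustering alone.** D = 1 + (m − 1) × ICC stays at or below 1.95 only if the district ICC is at most 0.95/163 = 0.0058 (m = 164) or 0.95/248 = 0.0038 (m = 249).

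**Step 4. Both levels.** Keep 0.05 as the total correlation within a surgery of k patients, and let a part r of it lie between districts. Then

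D = 1 + (k − 1) × 0.05 + (m − k) × r, and SE = 2 × √D × √(1/n₁ + 1/n₂).

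Power for 0.5 comes from the normal approximation, from the noncentral t with 4 df (six units, unpaired), and from the noncentral t with 2 df (three pairs). The range for r is an assumption, since the article gives no district ICC. Unit sizes are taken as equal, and no gain from matching is assumed.

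984 analysed, k = 20, m = 164:

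| District ICC r | D | SE | Normal | 4 df | 2 df |
|---|---|---|---|---|---|
| 0 | 1.95 | 0.178 | 80% | 57% | 35% |
| 0.005 | 2.67 | 0.208 | 67% | 45% | 28% |
| 0.02 | 4.83 | 0.280 | 43% | 28% | 19% |
| 0.05 (all between districts; worst case) | 9.15 | 0.386 | 25% | 17% | 12% |

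**Step 5. Recruited sample less 20%.** 654 × 0.8 ≈ 523 and 840 × 0.8 = 672, total 1195, m ≈ 199. Power with 4 df for r = 0 to 0.02 depends on the surgery size assumed:
- k = 20: D = 1.95 to 5.53, power 64% to 29%.
- k = 1195/96 ≈ 12.45: D = 1.57 to 5.31, power 73% to 30%.

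**Step 6. Detectable difference at 80% power, planned size, 4 df.** The required ratio of difference to SE is about 3.76, so 3.76 × 0.178 = 0.67 at r = 0 and 3.76 × 0.280 = 1.05 at r = 0.02.

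**The case against.** **The ICC of 0.05 was not stated for districts.** It is paired with clusters of 20, and a district ICC may be much smaller. This stands. A reader might carry 0.05 over to the districts and infer that the trial has 12% to 25% power, or that the effective sample can never exceed 3/0.05 = 60 per arm. The document does not support that: those figures are a worst case. At a district ICC of 0.005 the same cap is 3/0.005 = 600, above the 252 needed.

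**The analysis may not be a test on six units.** Mixed models are planned, the Discussion prefers evaluation at patient level, and the random-effect level and degrees of freedom may be settled in an analysis plan that is not shown. With zero district ICC and surgery-level degrees of freedom, power is about 80% at the planned size and about 93% for the recruited sample less 20% at 12.45 per surgery. This is the favourable end of the range and belongs in it. But nothing in the article supports a district ICC of zero, and matching districts on population characteristics suggests that they were expected to differ.

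**Matching and covariates could recover power.** They could, so the 2-df figures are not best estimates. Unequal unit sizes would work the other way. The sample size calculation credits neither.

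**The limitation is acknowledged.** It is in part: the Discussion mentions cluster effects but not the number of randomised units, and it leaves the power statement alone.

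A reader might also infer an arithmetic mistake; Step 1 shows that there is none. Nor does the smallest two-sided p of 0.25 for a pure randomisation test over 2³ = 8 allocations matter here, since no such test is planned.

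**Conclusion.** The point holds as a mismatch between the sample size calculation and the design. The 80% is stated without conditions, yet the cluster size behind it is not that of the randomised unit. At the planned size it needs two unstated conditions: an effectively zero district ICC, and degrees of freedom taken from surgeries or patients. If either fails, power is lower. Over an assumed district ICC of 0 to 0.02, it runs from 80% to 43% (normal), 57% to 28% (4 df) or 35% to 19% (2 df, no gain from matching). The true value within this range cannot be fixed from the document, so it would be as unsupported to assert that the trial has very low power as to assert 80%.

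This needs correcting, because the power for the primary endpoint does not describe the trial that was randomised.

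**What to change.** In Data management and calculation of sample size:
- name the level of the cluster of 20;
- replace the unconditional 80% with a calculation on the six randomised units, with surgeries nested and 4 or 2 degrees of freedom;
- report power for 0.5 points and the detectable difference over a range of district ICCs, stating the surgery size used;
- state the condition under which 80% would hold.

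In the Discussion, add that the number of randomised units limits precision, and that a non-significant result must not be read as coming from a trial with 80% power.

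Randomisation and recruitment are complete, so the number of units cannot change. The cost is recalculation and rewording, with no new patients. The downside is a less favourable stated power.
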